### Exercise interventions

#### High-speed resistance training (HSRT)

Participants who are randomized to the HRST will receive an exercise program that includes six to eight exercises targeting the lower limbs, to be performed twice a week for 8 weeks. The exercise sessions will be delivered by a qualified exercise physiologist or physiotherapist. The exercise program will include the following exercises: leg press, squat, step-up, lunges, going up stairs, sit to stand, calf raises (Table 1). Participants will be instructed to perform the exercises in a rapid and explosive manner such that all repetitions for each shortening phase (concentric activation of the muscle) will be performed as quickly as possible while the lengthening phase of the muscle (eccentric phase) will be controlled over 2–3 s. Several previous research trials have used similar principles of a high-speed training program for older people and those with knee OA and reported the training to be beneficial for older people, safe and with no adverse events [12–14]. However, none of the above studies investigated the effect of high-speed power training on balance or physiological risk factors for falls in this patient group, nor did they include functional weight-bearing exercises.

**Table 1 Tab1:** Details of the exercises and progression of the high-speed resistance program in the three phases

Exercise	% 1RM	Sets × repetitions	Progression
Phase 1 – week 1–2 (4 sessions)			
Bilateral leg press	20–40%	2 × 8–12	Load to be increased by 5–10% (of 1RM or % of BW) once participant reaches the upper limit of repetitions during their last set of each exercise with correct technique and velocity of contraction. All weight-bearing exercises will begin using bodyweight only ^a^height of chair/step adjusted to participant’s ability
^a^Step up		2 × 8–12	
^a^Sit to stand		2 × 8–12	
Calf raise		2 × 8–12	
Phase 2 – week 3–5 (6 sessions)			
Bilateral leg press	40–60%	2 × 5–8	Load to be increased by 5–10% (of 1RM or % of BW) once participant reaches the upper limit of repetitions during their last set of each exercise with correct technique and velocity of contraction. All weight-bearing exercises will begin using bodyweight only
^a^Step up		2 × 5–8	
^a^Sit to stand		2 × 5–8	
Calf raise			
^b^Squat		2 × 5–8	
^b^Stair climbing		2 × 5–8	
^b^Lunge		2 × 5–8	
Phase 3 – week 6–8 (6 sessions)			
Bilateral leg press	60–80	2–3 × 2–5	Load to be increased by 5–10% (of 1RM or % of BW) once participant reaches the upper limit of repetitions during their last set of each exercise with correct technique and velocity of contraction. All weight-bearing exercises will begin using bodyweight only
Step up		2–3 × 2–5	
Sit to stand		2–3 × 2–5	
Calf raise		2–3 × 2–5	
^b^Squat		2–3 × 2–5	
^b^Stair climbing		2–3 × 2–5	
^b^Lunge		2–3 × 2–5	

*1RM*, one repetition maximum, *BW* body weight

^a^height of chair/step adjusted to participant’s ability

^b^exercises to be added if participant is able to perform safely (in Phase 2 from week 4 onward)

#### High-speed resistance and balance training (HSRTB)

Participants who are randomized to the HRSTB will receive the same exercises as the HSRT group with the addition of six balance exercises. The balance exercises will include the following: walking forward and backward, single leg standing, single leg tapping, side stepping and backward walking. Progression of the balance exercises will include decrease in base of support, decrease in hand support and reduced sensory input (e.g., eyes closed). Each balance exercise will initially be of 15–30 s duration and be performed twice per session. Balance exercises are detailed in Table 2.

**Table 2 Tab2:** Details of the balance exercises and exercise progression

Exercise	Description	Sets/Reps/Time	Progression
1. Single leg balance – firm surface 10 s	Participant stands on one leg to balance with hands on hips Leg in air must not contact stance leg, floor or any other object to aid in balance	2 × 10 s	1. Increase time by 5 s increments (after performed same time 2 consecutive times) 2. Reach up to 30 s 3. Foam surface starting 10 s 4. Increase 5 s with progression 5. Repeat steps 1–4 commencing with eyes closed
2. Walking forward – tandem on firm surface (in between parallel bars)	Participant stands in between parallel bars Place one foot directly in front of the other (heel to toe) so they form a straight line	4 × lengths of parallel bars	1. Walking forward tandem on firm surface 2. Toe walking on firm surface turn on toes at end 3. Repeat steps 1–3 on foam 4. Repeat steps 1–3 eyes closed
3. Walking backwards – tandem on firm surface (in between parallel bars)	Participant stands in between parallel bars Place one foot directly behind the other (toe to heel) so they form a straight line	4 × lengths of parallel bars	1. Walking backward tandem on firm surface 2. Toe walking on firm surface 3. Repeat steps 1–3 on foam 4. Repeat steps 1–3 eyes closed
4. Side step walking (in between parallel bars)	Stand up tall and place hands on hips Take 10 side steps to the right Take 10 side steps to the left	4 × lengths of parallel bars	1. Side step walking firm surface 2. Side step walking with 1 obstacle in the middle 3. Side step walking with 2 obstacles 4. Continue to progress like this until every step is over an obstacle 5. Side steps with grapevine 6. Repeat steps 1–5 on foam 7. Repeat steps 1–5 with eyes closed
5. Single leg tap – clockwork (forward, lateral, behind) on firm surface	Standing on one leg Reach out to do clockwork starting with forward, lateral and backward tap Bring foot back down to standing Repeat starting from backward, lateral and forward tap.	2 × 5 forward, lateral, backward tap 2× backward, lateral, forward tap	1. 2 × 5 taps bringing foot back to midline in between each tap out 2. 2 × 5 taps not bringing foot back to midline 3. 2 × 5 and include tap on opposite side (cross shape) 4. Repeat steps 1–3 with stance foot on foam 5. Repeat steps 1–3 with eyes closed

Single leg exercises to be performed on each leg

## Exercise protocol and familiarisation sessions

Participants will undergo up to two familiarisation sessions prior to commencement of the intervention to ensure that they feel comfortable with the exercises and perform them with the correct technique. To determine the training load (resistance weight to be lifted) for the high-speed resistance-training exercises for each participant, an estimation of their one repetition maximum (or 1RM) will be calculated indirectly using submaximal estimation [15]. Participants will perform between 7 and 10 repetitions of each exercise with the maximum weight that they could lift. Participants performing the weight-bearing exercises (such as sit to stand, squat, calf raises) will initially use their body weight only. Additional weight (using a vest weight) will then be added as needed. Their estimated 1RM will be then used to determine the relative load/resistance required for the training protocol as detailed below.

### Exercise progression protocol

Each session will include a 5-min warm-up on a fitness bike or treadmill before commencement of the program and a 5-min cool-down of stretches of relevant muscles.

The 8-week program will be divided into the following phases to allow gradual progression and increase of the resistance for the high-speed resistance-training exercises (weight/training load) as detailed in Table 1:Phase 1 – weeks 1–2 (four sessions). Participants will perform two sets of 8–12 repetitions with 20–40% 1RMPhase 2 – weeks 3–5 (six sessions). Participants will perform two sets of 5–8 repetitions with 40–60% 1RMPhase 3 – weeks 6–8 (six sessions). Participants will perform two to three sets of 2-5 repetitions with 60–80% 1RM

The principle of progressing the exercise program will be similar to previous research in older people [11] as follows: for phases 1 and 2, the resistance/load will be increased by 5–10% of 1RM when the number of repetitions a participant will be able to perform (with correct technique at the required speed) will be more than eight in their last set. Similarly, in phase 3, the resistance/load will be increased (by 5–10% of 1RM) when the number of repetitions performed (with correct technique at the required speed) is five in the last set. Rest periods of 2–3 min will be given between sets.

Progression of the exercise will also be dependent on the individual perception of the difficulty of exercise (exercise intensity) and the level of pain as detailed below:

The 20-point Borg Rating of Perceived Exertion (RPE 6–20) scale will be used to determine the individual perception of difficulty of the exercises [16]. The RPE will be used to determine the intensity of each exercise where participants will be encouraged to exercise with a RPE of between 11 and 15/20. Increase in the training load will be made when a RPE of below 10/20 (“too easy/light”) will be reported by the participant.

The level of pain will also be recorded using the 0 to 10-point Numerical Pain Rating Scale (NRS; 0 –“no pain” to 10 – “worst possible pain”) for each exercise and will allow the load to be adjusted if the pain reported is too high [17]. Mild to moderate pain is expected in people with knee OA while exercising. However, substantial increases in pain may suggest that modifications to the exercise program are required [18]. A pain level of 7 and above will be deemed as too painful and load adjustment will be made.

### Pain-level documentation, exercise-stopping rules and adverse events

Pain level will be recorded using the NRS (0–10) during the sessions, 2 h and 24 h later. Any substantial increase in pain will be recorded. Pain-relief medication usage will be recorded via logbook by the participants during the intervention period.

The present study protocol will use similar principles to record pain and safety as reported in a previous dose-response trial in people with knee OA [19]. Substantial increases in pain will be defined as knee pain of at least 7/10 and or pain increased by at least 2–3/10 points (3/10 if initial pain is between 0 and 6/10 and 2/10 if initial pain is between 7 and 8/10) during the sessions, 2 h and 24 h after an exercise session as detailed below. The thresholds of 3/10 and 2/10 are based on a previous study suggesting that 2/10 represents a clinically significant change in pain and varies depending on the initial level [20].

An exercise-stopping rule will be defined as an incident (due to substantial increase in pain or an adverse event) that stopped the participant from completing the prescribed exercise for safety reasons and is likely to be related to the exercise program [19].

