#### Substantial knee pain levels during an exercise session

A pain level increase during an exercise to more than 7 or an increase in 3 points (if initial pain is between 0 and 6/10) will result in reducing the exercise load. If, after reducing load, the pain level remains at 7 or above, the specific exercise will be stopped. The specific exercise will be attempted again in the next session and the same rules will be applied. If stopped again, an *adverse event* will be deemed to have occurred and the exercise will no longer be practiced by the participant.

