#### Substantial knee pain levels after an exercise session (2 h and 24 h post session)

If a participant reports to the investigator a substantial amount of pain (as defined above) more than 2 h after an exercise session which lasts longer than 24 h, the exercise program will be reviewed and load will be reduced. If a substantial increase in pain occurs again in the next session, an *adverse event* will be deemed to have occurred and the exercise program will be reviewed and modified.

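### The pain cut-off is 7 or above in three rules but more than 7 in the load-reduction step and the reporting rule, so rises from 5 or 6 to exactly 7 go uncounted (minor)

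*Protocol article*

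**What the plan says.** Five statements in the protocol article set a cut-off on the 0–10 pain scale.

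- **Exercise progression protocol**, load adjustment: "A pain level of 7 and above will be deemed as too painful and load adjustment will be made".
- The definition, under **Pain-level documentation, exercise-stopping rules and adverse events**: "Substantial increases in pain will be defined as knee pain of at least 7/10 and or pain increased by at least 2–3/10 points". The size of the rise depends on the starting score: "3/10 if initial pain is between 0 and 6/10 and 2/10 if initial pain is between 7 and 8/10".
- **Substantial knee pain levels during an exercise session**, load-reduction step: "A pain level increase during an exercise to more than 7 or an increase in 3 points", the 3-point clause applying to initial pain of 0 to 6.
- **Same section**, stop step: "If, after reducing load, the pain level remains at 7 or above, the specific exercise will be stopped". The exercise is tried again next time ("The specific exercise will be attempted again in the next session and the same rules will be applied"), and a second stop counts as an adverse event.
- **Statistical analysis approach**, reporting: a substantial increase is tallied when pain goes above 7/10 or rises by 3 points.

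The first, second and fourth include a score of 7. The third and fifth exclude it unless the rise is at least 3 points. Exercises stopped due to pain and adverse events are listed among the primary feasibility and safety measures.

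**The concern.** Exactly 7 is an ordinary score on an 11-point scale, and the rules disagree about it. The section on pain during a session is also out of step with itself. Its load-reduction step starts above 7, yet the next sentence stops the exercise if pain stays at 7 or above, which suggests that 7 was meant to be inside the trigger.

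Safety is a main question of this pilot, so the threshold for calling pain substantial should be the same where it is defined, acted on and reported. If it is not, the published tally of substantial increases does not follow the protocol's own definition. Staff who consult only the section on pain during a session might also miss a load adjustment that another section requires.

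**Working it through.** **Inputs.** Let *b* be initial pain and *s* the pain reached, both whole numbers from 0 to 10. The graded rise *g* is: *s* − *b* ≥ 3 when *b* ≤ 6, or *s* − *b* ≥ 2 when *b* is 7 or 8. There is no planned figure to reproduce, so the check applies each rule to every rise (*s* > *b*). There are 11 × 10 / 2 = 55 of them.

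**Rules as written, for rises**

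| Rule | Condition | 4→7 | 5→7 | 6→7 | 6→8 |
|---|---|---|---|---|---|
| Load adjustment (Exercise progression protocol) | *s* ≥ 7 | yes | yes | yes | yes |
| Definition, read as *or* | *s* ≥ 7 or *g* | yes | yes | yes | yes |
| Load-reduction step | *s* > 7, or *s* − *b* ≥ 3 with *b* ≤ 6 | yes | no | no | yes |
| Reporting rule | *s* > 7, or *s* − *b* ≥ 3 | yes | no | no | yes |

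The stop step is not in the table because it applies after a load reduction. Its condition is *s* ≥ 7.

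**Counts**

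- Definition (*or*). Rises to 7, 8, 9 or 10: 7 + 8 + 9 + 10 = 34. Rises of at least 3 points ending at 3, 4, 5 or 6: 1 + 2 + 3 + 4 = 10. Total 44.
- Reporting rule. Rises to 8, 9 or 10: 8 + 9 + 10 = 27. Rises of at least 3 points ending at 3 to 7: 1 + 2 + 3 + 4 + 5 = 15. Total 42.
- Load-reduction step: the same 42. The only 3-point rise from above 6 is 7→10, which already exceeds 7.
- Difference: 44 − 42 = 2, namely 5→7 (2 points) and 6→7 (1 point). Rises to 7 from 4 or lower are caught everywhere by the 3-point clause.

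The reporting rule omits the 2-point clause for initial pain of 7 or 8. This changes nothing, because a 2-point rise from 7 or 8 already ends above 7.

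**Other readings of the definition.** Its connective is loose.

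- Read as *and* (*s* ≥ 7 and *g*), it flags 5 + 6 + 8 + 9 = 28 rises. It then agrees with the reporting rule at 5→7 and 6→7 but differs on 42 − 28 = 14 other rises.
- Read as *or* with no rise required, it also takes in 10 pairs where pain is 7 or above but unchanged or lower, giving 44 + 10 = 54 of the 121 possible pairs.

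The different cut-offs in the Exercise progression protocol and the load-reduction step do not depend on this choice.

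**After changing to at least 7 in the load-reduction step and the reporting rule.** Each flags 42 + 2 = 44 rises, the same ones as the definition read as *or*. No rise is then split.

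These are counts of possible classifications, not event rates. Starting scores of 5 or 6 are plausible, since eligibility requires average pain of at least 3.

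**The case against.** The strongest reply is that the Exercise progression protocol settles how a score of 7 is managed. Its load rule is unconditional and binds the same staff in the same session. The load-reduction step says what a rise above 7 leads to. It does not say that load is reduced only then, and it does not cancel the other rule. Read together, 5→7 leads to load adjustment, and the stop step follows if pain stays at 7. The general definition points the same way: "An exercise-stopping rule will be defined as an incident (due to substantial increase in pain or an adverse event" rests on substantial increase, which already includes 7. This stands.

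It limits a stronger conclusion that a reader might draw. Suppose an exercise takes pain from 5 to 7 in two consecutive sessions, and pain would remain at 7 after any load cut. Applying both sections gives 2 stops and 1 adverse event. Applying the load-reduction step alone gives none, because 7 is not more than 7 and 7 − 5 = 2 is below 3. One could infer that the primary safety counts are ambiguous and that the rules cannot be reconciled. The documents do not support that: the second result arises only if staff disregard the load rule. For session management the cumulative reading works.

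A reader might also want to rewrite the definition so that 7 counts only when pain has risen. That goes beyond aligning a cut-off. Against the literal *or* reading it would cut the definition from 54 pairs to 44, and it would make the 2-point clause for initial pain of 7 or 8 redundant. The rule for pain after a session relies on that definition ("a substantial amount of pain (as defined above) more than 2 h after an exercise session"), and a repeat there is an adverse event, so the rewrite could narrow adverse-event capture.

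The reply does not remove two things. The reporting rule still leaves out rises that the definition includes, and the load-reduction step still does not match the stop step that follows it.

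**Conclusion.** The concern holds as a minor inconsistency. With the definition read as *or*, rises from 5 or 6 to exactly 7 are substantial by definition but are not tallied as such in the descriptive pain analysis. That undercount follows from the wording alone, whenever such rises occur. The load-reduction step also fails to list them, although load adjustment is required elsewhere and the stop step includes 7. Different stop and adverse-event counts would follow only if staff applied the section on pain during a session in isolation.

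The size is 2 of 55 possible rises. The documents give no pain distribution, so the number of events in a trial of 30, with 20 in the two exercise groups, cannot be estimated. Reporting here is descriptive, the pain scores themselves are also to be summarised, and no test or sample size changes. The conclusion assumes whole-number scores and the *or* reading. Under *and*, these two rises would not be substantial, but 14 others would separate the definition from the reporting rule, and the load-reduction step would still differ from the Exercise progression protocol.

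**What to change.** Replace more than 7 with at least 7 in two places: the load-reduction step under Substantial knee pain levels during an exercise session, and the reporting rule under Statistical analysis approach. Leave the load rule in the Exercise progression protocol, the definition of substantial increase, and the rules for pain after a session as they are.

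The cost is a few words and no new data. Recruitment is described as ongoing, so remaining sessions can follow the aligned wording. Sessions already held can be re-tallied from the recorded scores, provided the initial score was kept.

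The downside is that 5→7 and 6→7, the latter only a 1-point rise, now count as substantial, so the reported count may be slightly higher. Steady pain at 7 or above with no rise remains outside the reporting line, which concerns increases. It still leads to load adjustment under the Exercise progression protocol.

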#### Substantial knee pain levels during an exercise session

A pain level increase during an exercise to more than 7 or an increase in 3 points (if initial pain is between 0 and 6/10) will result in reducing the exercise load. If, after reducing load, the pain level remains at 7 or above, the specific exercise will be stopped. The specific exercise will be attempted again in the next session and the same rules will be applied. If stopped again, an *adverse event* will be deemed to have occurred and the exercise will no longer be practiced by the participant.

#### Substantial knee pain levels after an exercise session (2 h and 24 h post session)

If a participant reports to the investigator a substantial amount of pain (as defined above) more than 2 h after an exercise session which lasts longer than 24 h, the exercise program will be reviewed and load will be reduced. If a substantial increase in pain occurs again in the next session, an *adverse event* will be deemed to have occurred and the exercise program will be reviewed and modified.

##### Serious adverse events

The following circumstances will be considered as serious adverse events: any report of difficulty in breathing that does not settle quickly with rest; new or unrelenting chest pain; or acute changes in level of consciousness during the session. A serious adverse event will be defined if symptoms have not settled and a medical emergency procedure will be required.

### Control group

During the 8 weeks, participants from the control group will be advised to continue with their usual activities. Usual activities will be defined as any normal day-to-day activities and or any current usage of health services.

## Outcome measures

### Feasibility and safety outcomes (primary measures)

Data for feasibility and safety will be analyzed as follows: percentage of participants who complete the intervention, overall percentage of sessions attended, number of participants who dropout due to reasons related to the exercise program or the overall research project, number of sessions and or number of exercises stopped due to pain, any adverse event or incident that stops the participant from completing the prescribed exercise.

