## Statistical analysis approach

Data collected for feasibility and safety will be analyzed using descriptive statistics (mean, standard deviation, and proportion) as follows: the percentage of participants who complete the intervention, overall percentage of sessions attended, number of participants who dropout, number of sessions and or number of exercises stopped due to pain, and any adverse event or incident that prevented the participant from completing the prescribed exercise.

Reported pain level will also be analyzed using descriptive statistics as follows: pain level during the exercise program, 2 h and 24 h after a session, any substantial increase in pain level to more than 7/10 or increase by 3 points, and overall pain level before, and at the completion of, the program.

To determine statistical trends of effectiveness, analyses of the selected outcomes, such as pain, strength, balance, physical function and executive functions, will be performed to assess the changes within and between groups over time (pre-post). Therefore, repeated measure analysis of variance (ANOVA) with factors of intervention (HSR, HSRTB, control) and time (pre-post intervention) will be used. This data will be used to determine power calculations for a fully powered future trial on the main outcomes investigated.

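### Exercises stopped for pain are counted without a denominator, although HSRTB performs about 1.6 to 2.5 times as many exercises as HSRT, so the counts cannot show whether balance work changes tolerance of the resistance exercises

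*Protocol article*

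**What the plan says.** Under Feasibility and safety outcomes (primary measures), completion and attendance are given as percentages. Pain stops are given as the "number of sessions and or number of exercises stopped due to pain". Statistical analysis approach repeats that wording, under a general statement that the data will be described by means, standard deviations and proportions.

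The in-session rule acts on the individual exercise. If pain stays high after the load is reduced, that exercise is stopped. Then: "The specific exercise will be attempted again in the next session and the same rules will be applied". A second stop is declared an adverse event and the exercise is dropped for that participant (Substantial knee pain levels during an exercise session). Pain is scored "for each exercise and will allow the load to be adjusted if the pain reported is too high" (Exercise progression protocol).

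The two exercise arms attend the same 16 sessions (Procedure). HSRT receives "an exercise program that includes six to eight exercises targeting the lower limbs, to be performed twice a week for 8 weeks". HSRTB participants "will receive the same exercises as the HSRT group with the addition of six balance exercises".

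In-session pain is to be described as "pain level during the exercise program, 2 h and 24 h after a session". The level of summary (exercise, exercise type or session) is not stated.

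**The concern.** The arms differ, by construction, in how many exercises can be stopped. The control group has no exercises to stop, so the only between-arm reading of this measure is HSRT against HSRTB. The stated aim covers the program with and without balance exercises, and the Background says it is crucial to know what the high-speed resistance work does to knee pain.

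A higher stop count in HSRTB could mean that the resistance exercises are tolerated less well when balance work is added. It could equally mean only that more exercises were attempted. An undivided count cannot separate the two. With 10 participants per arm and purely descriptive reporting, readers will compare the two totals directly, and the choice of program for the larger trial could rest on that comparison.

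**Working it through.** **Inputs**
- Sessions: 2 per week × 8 weeks = 16. Table 1 agrees: 4 + 6 + 6 = 16.
- Resistance exercises, text: six to eight, although the list that follows names seven ("leg press, squat, step-up, lunges, going up stairs, sit to stand, calf raises (Table 1").
- Resistance exercises, Table 1: four in Phase 1 and four to seven afterwards. Squat, stair climbing and lunge are "exercises to be added if participant is able to perform safely (in Phase 2 from week 4 onward".
- Balance exercises: six in the text, five in Table 2.

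The text counts are not reproduced by the tables, so both are carried through.

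**Exercises per session, HSRTB / HSRT**
- Text: (6 + 6)/6 = 2.00 to (8 + 6)/8 = 1.75.
- Tables: (4 + 5)/4 = 2.25 to (7 + 5)/7 = 1.71.
- Mixed extremes: (8 + 5)/8 = 1.62 to (4 + 6)/4 = 2.50.

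**Exercise occasions per participant over the course** (full attendance, no exercise dropped)
- R, the resistance occasions by Table 1:
  - low: 4×4 + 2×4 + 4×4 + 6×4 = 64
  - high, optional exercises from week 4: 4×4 + 2×4 + 4×7 + 6×7 = 94
- B, the balance occasions: 16×5 = 80 or 16×6 = 96.
- HSRTB total: 64 + 80 = 144 up to 94 + 96 = 190. Ratios run from (94 + 80)/94 = 1.85 to (64 + 96)/64 = 2.50.
- With the text's resistance counts, R is 96 to 128. The ratios run from (128 + 80)/128 = 1.62 to (96 + 96)/96 = 2.00.

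**Effect on stop counts when resistance exercises carry the same risk in both arms**

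Let p be the stop risk per resistance occasion and f the risk of a balance occasion relative to it. Neither is in the document. Then:
- ratio of raw counts = (R + fB)/R = 1 + fB/R
- ratio of rates over all exercises = (R + fB)/(R + B)

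The value of p cancels. A ratio of 1.0 would correctly show no difference in tolerance of the resistance work. Ranges cover R = 64 to 94 and B = 80 or 96:

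| f (assumed) | Raw-count ratio | All-exercise rate ratio |
|---|---|---|
| 0 | 1.00 | 0.40–0.54 |
| 0.25 | 1.21–1.38 | 0.55–0.66 |
| 0.5 | 1.43–1.75 | 0.70–0.77 |
| 1 | 1.85–2.50 | 1.00 |

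Example with p assumed to be 2%, R = 94, B = 80 and 10 participants per arm:
- HSRT expects 10 × 94 × 0.02 = 18.8 stops.
- HSRTB expects 18.8 at f = 0.
- HSRTB expects 10 × (94 + 0.25×80) × 0.02 = 22.8 at f = 0.25.
- HSRTB expects 10 × 174 × 0.02 = 34.8 at f = 1.

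So the raw count is fair to the resistance component only at f = 0, and the all-exercise rate only at f = 1.

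**In-session adverse events.** An exercise stopped a second time is no longer practiced, so each exercise can yield at most one such event per participant. By the tables the ceiling is 7 in HSRT and 7 + 5 = 12 in HSRTB, a ratio of 1.71.

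**Measures with equal opportunity.** The post-session adverse-event rule and the 2 h and 24 h pain scores work per session, and both arms have 16 sessions.

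**The case against.** The strongest reply is that the added exercises are the HSRTB intervention. If they bring more stops per participant, that is a real burden of the program and is what a feasibility pilot should report. This stands. A reader might infer that the safety comparison is distorted by design; the documents do not support that. Raw totals answer the program-level question correctly, safety is descriptive, the stated comparator is control, and no HSRT-versus-HSRTB harm test is planned.

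A near-doubling also needs balance exercises to provoke stops as often as explosive resistance work. That is doubtful: the stop follows a reduction in load, and Table 2 describes no load. Dropping an exercise after a repeat stop further limits repeated stops. This also stands, and is why the size is given as a range starting at no inflation.

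A reader might further infer that in-session pain is averaged over all exercises, so that milder balance exercises would dilute the HSRTB mean. The text does not say so. Pain is recorded for each exercise and the level of summary is left open.

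Finally, it can be said that denominators are table layout, normally left to a fuller document, and that proportions are among the named statistics. This does not dispose of the point. The article fixes the form of each primary measure and words stops as a number, next to two measures worded as percentages.

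**Conclusion.** The point holds for two measures: the number of exercises stopped for pain, and the adverse events declared under the in-session rule. Both accrue per exercise, while HSRTB performs about 1.6 to 2.5 times as many exercises as HSRT across all combinations of the stated counts. With equal risk on the resistance exercises, the raw-count ratio for stops lies between 1.0 and 1.85–2.5 by the table schedule, depending on the unknown relative risk of balance exercises. A single all-exercise denominator errs the other way, down to 0.40–0.54 if balance exercises never cause a stop. These figures assume full attendance, no dropped exercises and a common risk across resistance exercises.

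The point does not extend to post-session adverse events or to pain at 2 h and 24 h. This is a cheap improvement to the reporting of a primary safety measure; it does not invalidate the plan.

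**What to change.** In Feasibility and safety outcomes (primary measures) and in Statistical analysis approach:

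1. Report, by arm, pain stops and in-session pain adverse events on the resistance exercises common to both arms, with stops expressed per exercise attempted.
2. Report the balance exercises separately, within HSRTB only.
3. Summarise in-session pain with the same split.
4. Keep raw totals per participant as a description of program burden.

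Reconcile the exercise counts, because they set the denominator: six to eight in the text against four to seven in Table 1 for resistance, and six against five in Table 2 for balance.

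Pain is already scored for each exercise and stops are already exercise-specific, so the change is to wording, plus a few more table rows.
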